### 10.3. Efficacy Analyses

#### 10.3.1. Analysis of the Primary Efficacy Variable

The primary efficacy data will be analyzed by using the ITT.

The percent of subjects attaining a platelet count of  $\geq 50 \times 10^9/L$  by Day 9 will be compared with the historical response rate of  $>60\%$ . A 1-sided 95% confidence interval will be constructed for the percent of subjects attaining a platelet count of  $\geq 50 \times 10^9/L$  by Day 9 for GAMMAPLEX. If the lower bound of this confidence interval is  $>0.60$ , GAMMAPLEX will be declared effective for the treatment of chronic ITP.

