## 10. STATISTICAL METHODS

### 10.1. Sample Size

The calculation of sample size was based on the primary efficacy variable, i.e., the percent of subjects attaining a platelet count of  $\geq 50 \times 10^9/L$  by Day 9 on the first course of GAMMAPLEX. A minimum of 31 evaluable subjects will be enrolled in the study. However, when 27 evaluable subjects have completed Day 9, a partial analysis may be conducted, and the response rate ( $P_1$ ) calculated and compared with that of the historical control,  $P_0$  (lower bound of 95% confidence interval) is greater than 0.60, to determine the power achieved at this interim stage. The response rate estimated at this stage will be used to re-estimate the sample size necessary at the end of the study to achieve a power of 80% to detect the desired difference.

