### **10.5.1. Interim Analysis**

An interim analysis may be performed when at least 30 evaluable adult subjects have completed Day 32. All other subjects recruited up to this time point, e.g. non-evaluable subjects or children (applicable to subjects enrolled before implementation of Protocol Version 7) will be analyzed for safety only. The purpose of this analysis is to facilitate submission of an application to the U.K. and EU regulatory authorities (22).

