### **10.5.2. Partial Analysis**

A partial analysis may be performed when at least 27 evaluable subjects have completed Day 9. The observed response rate will be estimated and compared with the historical control of  $>0.60$  to re-estimate the sample size.

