## **15. REPORTING AND PUBLICATION**

### **15.1. Study Reports**

#### **15.1.1. Interim Clinical Study Report**

A complete study report, in accordance with ICH guidelines, may be prepared by the CRO after the 30th evaluable adult subject has completed Day 32. All other subjects recruited up to this timepoint, e.g. non-evaluable subjects or children (applicable to subjects enrolled before implementation of Protocol Version 7) will be analyzed for safety, and those who have completed Day 32 will also be included. This report may be used for submission to the U.K. and EU regulatory authorities.

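### Final N follows the response rate at 27 subjects without a maximum, and a submission report at 30 has no stated status under the efficacy rule, so the one-sided 5% level is not assured

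*Protocol*

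**What the plan says.** **Decision rule.** Section 10.3.1 and the synopsis state one rule. "A 1-sided 95% confidence interval will be constructed for the percent of subjects attaining a platelet count" at the threshold by Day 9, and the declaration is tied to that bound: "If the lower bound of this confidence interval is" above 0.60, the product is declared effective. No other efficacy criterion appears.

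**Partial analysis.** Section 10.5.2: "A partial analysis may be performed when at least 27 evaluable subjects have completed Day 9". Section 10.1 gives its use: "The response rate estimated at this stage will be used to re-estimate the sample size necessary at the end of the study", with a target power of 80%. Sections 5.2 and 10.1 give 31 evaluable subjects as a minimum. No maximum appears.

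**Interim analysis.** Section 10.5.1: "An interim analysis may be performed when at least 30 evaluable adult subjects have completed Day 32". Everyone else recruited by then is analysed for safety alone, so efficacy is evidently analysed in the 30. Section 15.1.1 provides for a full ICH-format report at that point and adds: "This report may be used for submission to the U.K. and EU regulatory authorities". Neither section names a test, a bound or a significance level, and neither says that the report cannot support an efficacy claim.

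**The concern.** This is an open-label, single-arm trial, and the bound in Section 10.3.1 is its only formal protection against a false claim of efficacy. Two features can erode it.

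First, the final N depends on the same responses that are later tested. A promising early rate stops the trial near 31. A middling rate extends it, possibly by a great deal.

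Second, a report that carries efficacy data into a marketing application comes before the final test. If a reader of that report applies the 0.60 rule, as the only rule the protocol offers, the product has two chances to pass at an unadjusted level. Both early analyses are optional, so the number of looks is also left open.

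**Working it through.** **Inputs from the protocol.** Null rate P0 = 0.60, one-sided 95% lower bound, 80% power target and minimum N of 31 (Sections 10.1 and 10.3.1). Looks at 27 and 30 (Section 10.5).

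**The stated 31.** It cannot be reproduced, because the difference to be detected is never quantified. With an exact (Clopper-Pearson) bound, 31 subjects need at least 24 responders. Power is 73.0% at a true rate of 0.80 and 81.8% at 0.82. A one-sided 5% normal approximation with null variance gives 33 at 0.80 and 30 at 0.81. So 31 fits an unstated rate a little above 0.80.

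**Single analyses, exact, true rate 0.60.** The error is P(X ≥ c), with c the smallest count whose lower bound exceeds 0.60.
- n = 30: c = 23, error 4.35%.
- n = 31: c = 24, error 3.30%.

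**Looks at 30 and 31 only.** Reaching 24/31 requires at least 23/30, so the final test adds nothing. The total is 4.35%, inside 5%.

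**Re-estimation.** Assumed rule, since the protocol gives no formula, with p the observed rate at 27:

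N = {[1.645·√(0.6·0.4) + 0.842·√(p(1−p))] / (p − 0.60)}², rounded up, not below 31 and not above an assumed maximum.

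- 22/27 (p = 0.815): (0.806 + 0.327)² / 0.215² = 27.8, so 28, raised to 31.
- 21/27 (p = 0.778): (0.806 + 0.350)² / 0.178² = 42.3, so 43.
- 17/27 (p = 0.630): (0.806 + 0.407)² / 0.0296², about 1,674.

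The last line shows what having no maximum means: a maximum of 1,700 is in effect uncapped. If p ≤ 0.60 the formula fails, and I let N be either 31 or the maximum. The ranges below cover both.

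**Enumeration.** Sum over x ~ Bin(27, 0.60), the next 3 subjects, then the remaining N − 30. The 27 are taken to be among the 30, and the 30 among the N.

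| Maximum N | Final test only | Rule at 30 and at the end |
|---|---|---|
| 40 | 3.9% | 5.6% |
| 60 | 4.8–4.9% | 6.7–6.8% |
| 100 | 4.8–5.2% | 6.8–7.2% |
| 1,700 | 5.3–7.4% | 7.3–9.4% |

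Error does not rise smoothly with the maximum, because the binomial is discrete. If N is instead re-estimated by exact power, the final-only figure is 5.03% at a maximum of 60 and about 5.6% at 100, both with continuation to the maximum when p ≤ 0.60.

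**With the proposed change.** A mark of 25/30 has exact one-sided p = 0.0057. Having 25/30 implies at least 22/27, hence N = 31 and a final mark of 24, already met. The interim mark therefore adds no error beyond the final test. With a maximum of 60 the total is 4.8% to 4.9%, and power is about 94% at a true 80%.

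**The case against.** The strongest reply is that the protocol never says its early analyses can declare efficacy. A reader might infer that all three analyses apply the one-sided 95% rule. The text does not support that: the rule is attached only to the primary analysis, and Section 10.5.1 names no bound. A reader might also count the look at 27 as a chance to claim, which would bring the total to 7.6% to 10.3% for maxima of 60 to 1,700. That does not stand either, because Sections 10.1 and 10.5.2 give that analysis one purpose, re-estimation.

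The upper figures also need an extreme case: 7.4% and 9.4% arise only if the trial runs to 1,700 subjects after an observed rate of 0.60 or less, which is implausible at about 25 sites. At modest maxima, re-estimation alone leaves the error near nominal.

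Figures of 12% to 14% can be produced with a normal-approximation bound, which alone gives 7.4% at N = 31. The protocol names no interval method, and that choice is commonly left to the statistical analysis plan, which is not shown. Those figures are not part of this point. The same plan might also allocate the error level.

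What remains is that the protocol itself creates the declaration rule, the response-driven N without a maximum, and the submission report at 30. Their relation to one another is a design matter, and on it the protocol is silent.

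**Conclusion.** The point holds in a conditional form. The protocol permits a route on which the one-sided 5% level is exceeded, and nothing in it closes that route. If the 30-subject report makes no claim and the final N stays modest, error is about 3.9% to 5.2% for maxima of 40 to 100. If the same rule is used at 30 and again at the end, it is about 5.6% to 7.2% for those maxima. It stays at 4.35% only when the final N is 31. With no effective maximum, both sets of figures are higher.

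These results assume exact bounds, a true rate of exactly 0.60, and re-estimation by the normal-approximation formula shown. They do not establish that the 5% level will be lost, since both early analyses are optional and the status of the interim report is unstated.

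**What to change.** Amend Sections 10.3.1 and 10.5 as follows.

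1. State that the 30-subject report is descriptive for the primary endpoint, or that a claim there requires at least 25/30 responders.
2. Set a fixed maximum of 60 for the re-estimated N. This figure carries the error control and should not be left as an example: at 100 the final test alone can reach 5.2%.
3. Write down the re-estimation formula and the action when the observed rate is 0.60 or less. With exact power instead of the normal approximation, the total can reach about 5.0%.
4. Compute the final bound exactly. The one-sided 95% rule can then stay.

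If no maximum is wanted, use exact one-sided 97.5% bounds at the interim and final analyses. Error is then at most about 4.5% in the cases computed. With N still re-estimated at one-sided 5%, power is about 93% to 94% at a true 80%.

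**Cost.** Mainly wording. Under the first option the interim pass mark rises from 23/30 to 25/30, and the chance of an interim claim at a true 80% falls from 76% to 43%, or to none if the report is descriptive. Under the 97.5% option the final test becomes stricter.

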#### 10.3.2. Analysis of the Secondary Efficacy Variables

- The method of Kaplan and Meier will be used to produce plots of the distribution of the time for which the platelet counts remain  $\geq 50 \times 10^9/L$ . A 95% confidence interval for the median time will be constructed.
- Each bleeding/hemorrhage event will be graded according to the criteria in Appendix 1 and analyzed by using descriptive statistics. Data will be summarized by number and percent.

## **10.4. Safety Analyses**

### **10.4.1. Adverse Events**

The number of infusions in which an AE occurs during an infusion or within 72 hours after the infusion stops will be tabulated. A summary table including the following will be produced:

- number of subjects with AEs
- number of subjects with SAEs
- number of subjects who died
- number of subjects who withdrew because of AEs
- number of subjects with product-related AEs.

The nature, severity and frequency of all AEs will be listed.

### **10.4.2. Other Safety Assessments**

Summary tables for the results of laboratory measures of hepatic, renal, and hematologic function will include the following:

- Descriptive statistics (mean, standard deviation, median, maximum and minimum) for original values and change from baseline for all continuous variables
- Incidence (number and percent) of clinically significant, treatment-emergent abnormal values (TEAVs)
- Shift tables showing the change from baseline in the incidence of new or worsening clinically significant findings.
- The number of subjects in whom there is a transmission of Hepatitis B, Hepatitis C, HIV, or Parvovirus B19 will be tabulated. The results from the Direct Coombs' Test and associated haptoglobin, LDH and urine hemosiderin will also be tabulated.

All abnormalities after baseline in the results of the physical examination will be summarized by using number and percent. Shift tables from normal to abnormal and abnormal to normal will also be produced.

Summary statistics (mean, median, standard deviation, maximum and minimum of original values, and change from baseline) for all vital sign measures, will be provided.

## **10.5. Interim/Partial Analyses**

There may be an interim analysis and a partial analysis performed during the study.

### **10.5.1. Interim Analysis**

An interim analysis may be performed when at least 30 evaluable adult subjects have completed Day 32. All other subjects recruited up to this time point, e.g. non-evaluable subjects or children (applicable to subjects enrolled before implementation of Protocol Version 7) will be analyzed for safety only. The purpose of this analysis is to facilitate submission of an application to the U.K. and EU regulatory authorities (22).

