If the subject is enrolled within 14 days of screening, all medications the subject is taking at the time of screening may be continued through the completion of the second infusion, including corticosteroids; however, the dose must remain unaltered through Day 9 unless some condition of the subject requires a change. If possible, doses of corticosteroids or other immunosuppressant medications should remain constant until Day 32 (see Section 6.1). All concomitant medications will be recorded on the CRFs.

If the subject is not enrolled within 14 days of screening, it should be noted that doses/regimen of corticosteroid must have been stable for 2 weeks prior to Day 1; and doses/regimen of azathioprine, cyclophosphamide, and attenuated androgens must have been stable for 2 months prior to Day 1. Changes to the dosage of these medications should be avoided as mentioned above. In addition subjects are not to receive an IGIV preparation or an investigational agent or

any blood, blood product or blood derivative within 1 month prior to Day 1, and receipt of any live virus vaccine and Rituximab is not allowed within 3 months prior to Day 1.

Administration of corticosteroids to decrease adverse reactions to the infusion may not be given before the IGIV infusions. However, pre-medication with analgesic or antihistamine drugs is permissible if required.

No blood products, including IGIV (other than GAMMAPLEX in accordance with the protocol), may be given during the study until the End of Study visit (viral safety visit approximately 3 months after the last dose of GAMMAPLEX).

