### 10.2. Analysis Population

Any subject who started treatment with GAMMAPLEX and whose central laboratory results taken prior to infusion on Day 1 are within specified protocol parameters, will be included in the intent-to-treat (ITT) population for analysis of efficacy and safety. Any subject whose central laboratory results from Day 1 are outside of the required parameters, will be included in the safety analysis only.

Additionally, subjects aged 6 to 17 years (applicable only to subjects enrolled before implementation of Protocol Version 7) will be analyzed separately from the remaining samples for any differences in response to treatment. This subset will be analyzed in the same manner as the total sample.

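### Read literally, the interim efficacy set drops treated ITT adults who withdraw before Day 32, in conflict with Sections 10.2 and 10.3.1

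*Protocol*

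**What the plan says.** Section 10.5.1 gives the trigger: "An interim analysis may be performed when at least 30 evaluable adult subjects have completed Day 32". The next sentence disposes of everyone else: "All other subjects recruited up to this time point, e.g. non-evaluable subjects or children" (the latter if enrolled before Version 7) are analyzed for safety only. The synopsis has the same two sentences. The stated aim is regulatory: "The purpose of this analysis is to facilitate submission of an application to the U.K. and EU regulatory authorities".

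Section 15.1.1 describes the interim report on the same trigger. It analyzes the other subjects for safety, without the word only, and adds that "those who have completed Day 32 will also be included". It also says: "This report may be used for submission to the U.K. and EU regulatory authorities".

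The general rules differ. Section 10.2 admits to the ITT population "Any subject who started treatment with GAMMAPLEX and whose central laboratory results taken prior to infusion on Day 1 are within specified protocol parameters"; no visit has to be completed. Section 10.3.1 states: "The primary efficacy data will be analyzed by using the ITT". Section 8.1 defines response as reaching a platelet count of at least 50 × 10⁹/L by Day 9.

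**The concern.** The primary outcome is settled by Day 9. If membership of the interim efficacy set depends on reaching Day 32, the primary result is conditioned on events that follow it. A treated adult with acceptable Day 1 laboratory results who withdraws on Day 12, say, is in the final ITT denominator but missing from the interim one, and another subject takes the place towards the 30.

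Such withdrawal need not be unrelated to response. Section 5.3.1.1 says: "No blood products, including IGIV (other than GAMMAPLEX in accordance with the protocol), may be given during the study until the End of Study visit". Section 5.3.1.4 requires discussion with the medical monitor and sponsor before a second course is given after Day 9 and before Day 32. A subject whose count stays low may therefore have a reason to leave. That mechanism is an inference from the protocol's rules; the protocol reports nothing of the kind. At stake is a response rate that may go to U.K. and EU authorities and may not match the ITT rate in the final report.

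**Working it through.** **Passages side by side.**

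| Question | Sections 10.2, 10.3.1 and 8.1 | Section 10.5.1 and synopsis, read literally |
|---|---|---|
| Who is in efficacy? | Treated, Day 1 central laboratory results within limits | Evaluable adults who completed Day 32 |
| When is response settled? | By Day 9 | Not restated |
| ITT adult who withdraws between Day 9 and Day 32 | Counted with the known outcome | Among the other subjects: safety only |
| ITT adult who withdraws earlier without a qualifying count | In the denominator, has not attained the threshold | Among the other subjects: safety only |

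Non-evaluable subjects and children are introduced as examples, so they do not limit who the other subjects are.

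**How far the rate could move.** The plan gives no interim figure to reproduce.

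Inputs from the protocol: 30 subjects (Section 10.5.1); a one-sided 95% interval and a lower bound above 0.60 (Section 10.3.1).

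Assumptions: the interval method, which the protocol does not name; the number of withdrawals, since no dropout rate is given; and the outcome of those who withdraw.

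Formulas, for x responders among n, p = x/n, z = 1.645:

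- Exact (Clopper-Pearson): L solves P(X ≥ x | n, L) = 0.05, which is the 5th percentile of Beta(x, n − x + 1).
- Wilson: L = [p + z²/(2n) − z·√(p(1−p)/n + z²/(4n²))] / (1 + z²/n).
- Wald: L = p − z·√(p(1−p)/n).

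| Case | x/n | Exact | Wilson | Wald |
|---|---|---|---|---|
| 23 respond, completers only | 23/30 | 0.606 | 0.621 | 0.640 |
| 1 non-responder restored | 23/31 | 0.582 | 0.597 | 0.613 |
| 1 responder restored instead | 24/31 | 0.617 | 0.632 | 0.651 |
| 24 respond, completers only | 24/30 | 0.643 | 0.657 | 0.680 |
| 2 non-responders restored | 24/32 | 0.594 | 0.608 | 0.624 |
| 25 respond, completers only | 25/30 | 0.681 | 0.695 | 0.721 |
| 3 non-responders restored | 25/33 | 0.605 | 0.618 | 0.635 |
| 4 non-responders restored | 25/34 | 0.584 | 0.597 | 0.611 |

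On the exact bound, 23/30 is the smallest count that clears 0.60 (22/30 gives 0.570). From there one restored non-responder takes the bound below 0.60; from 24/30 it takes two, and from 25/30 four. Wilson agrees for 23/31 and 25/34 but not for 24/32. Wald stays above 0.60 in every row. Restoring a responder raises the bound.

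**Extreme case in probability.** Suppose the ITT rate is exactly 0.60 and w further adults withdraw, all of them non-responders. The rate among completers is then 0.60 × (30 + w)/30, which is 0.60, 0.62, 0.64 and 0.66 for w = 0, 1, 2 and 3. The binomial probability of at least 23 responders in 30 is 0.044, 0.068, 0.102 and 0.148 respectively.

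**The case against.** The literal reading is not forced. The trigger sentence says when the interim may take place, and withdrawals are not among the examples of other subjects. The protocol's explicit route out of efficacy is the Day 1 central laboratory rule (Sections 5.3.1.1 onward to 6.3, and 10.2), and Section 10.2 also sends those subjects to safety only. If evaluable means just that, an adult who withdraws on Day 12 stays in ITT and there is no conflict. Section 15.1.1 is too loosely worded to decide the matter. This stands as a real ambiguity: evaluable is undefined and Day 32 may be timing only. But the sentence about all other subjects does not say so, and its plain words exclude these adults.

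Section 6.3 asks that a treated subject who withdraws still has the Day 32 and End of Study assessments if possible. Some who withdraw could thus complete Day 32. That reduces the loss without closing it. Section 5.3.1.4 also leaves open a second course before Day 32 after discussion, so leaving is not the only course for a subject with a low count.

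A reader might infer that the interim rate must be too high. The documents do not support that: a Day 9 responder who relapses may also leave, and excluding that subject lowers the rate. A reader might also infer that one or two withdrawals would overturn an interim verdict. Section 10.5.1 sets no interim success test; the 0.60 criterion belongs to Section 10.3.1, and the reversals occur only near the boundary and depend on the interval method.

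Fine detail of an interim set can be left to a SAP. Here, however, the protocol itself states a rule that departs from its own ITT definition.

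**Conclusion.** The point holds as an inconsistency in the protocol's wording that should be corrected. Read literally, Section 10.5.1 and the synopsis remove from interim efficacy treated ITT adults who withdraw before Day 32, against Sections 10.2 and 10.3.1 and with an endpoint settled at Day 9. The likely direction is upward, but that is a judgement.

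The size is modest and conditional. With assumed non-responding withdrawals and the exact bound, one is enough to matter at 23/30 and two at 24/30, while 25/30 withstands three; Wilson and Wald bounds are less sensitive. The population conflict does not depend on any of these figures.

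The defect is confined to the optional interim analysis and its report; the final primary analysis remains ITT. It should not be read across to the 27-subject partial analysis: Section 10.5.2 contains no safety-only rule. Adults still on study but not yet at Day 32 are also left out by the wording, but that is an ordinary data cut-off and less informative than withdrawal.

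**What to change.** In Section 10.5.1, Section 15.1.1 and the synopsis:

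- State that completion of Day 32 by 30 evaluable adults sets only the timing of the interim analysis.
- Define the interim efficacy set as all adults in the Section 10.2 ITT population whose first infusion was on or before that of the last subject counted towards the 30, whether or not they reached Day 32.
- Count any of them without a platelet count of at least 50 × 10⁹/L by Day 9 as a non-responder.

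The cost is wording in three places, with no extra subjects or visits. The small downside is that the interim response rate may be slightly lower.
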